#### Data Collection

Clinical data will be collected in a standardized way on a trial specific data form. Data will be transcribed from the patient’s notes or the clinical information system (Philips CareVue) by members of the PERMIT research team. Baseline measures of severity of illness (Acute Physiology and Chronic Health Evaluation II score, Sequential Organ Failure Assessment score) will be collected on admission, along with the demographics required to demonstrate equivalent groups.

All estimations of blood glucose and serum potassium, whether performed in the central laboratory or using near patient testing, will be collected from the clinical information system (CareVue). The doses of insulin, potassium, glucose, and antibiotics will also be collected. Nitrogen input will be estimated from the documented feed rates. Blood glucose levels will be monitored hourly, and 3-hydroxybutrate levels daily, using the Abbott system.

Blood and urine samples will also be taken from all randomized patients whilst they remain in the ICU. Specifically, blood samples will be taken at baseline (Day 1), Day 3, Day 5, Day 7 and Day 14. Urine collections will be taken over the preceeding 24-hour period on Days 3, 5, and 7.

Data are collected for the entire period of the patient’s stay in ICU. The hospital discharge date will be obtained from the local patient administration system (PAS) by the Trial Office. When a patient is transferred to another acute hospital, the discharge date will be requested from the receiving hospital. To enable collection of patient status 30 days after randomization, the PAS will be interrogated to determine the patient’s location at 30 days. For those patients that have been discharged, the patient’s General Practitioner will be contact by telephone to establish their location. There is no planned long-term follow up.

#### Statistical Analysis

The principal comparisons will be between those allocated to usual care and those allocated to mandatory insulin (the “intention to treat principle”). The primary outcome variable will be the differences in the number of hypoglycaemic and hypokalaemia events between groups which will be compared by chi-squared tests. Differences between multiply measured continuous variables will be compared using analysis of variance. To allow for differences in length of stay between patients, wherever possible, variables will be converted to time-weighted averages if they are used as a single, between-group measure.

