**Methods:**

This protocol summarizes the rationale and design of a randomized, controlled, single-center trial investigating the effect of mandatory insulin therapy versus usual care insulin therapy for those patients admitted for a stay of longer than 48 hours. In total, 109 critically ill adults predicted to stay in intensive care for longer than 48 hours consented. The primary outcome is to determine the safety of mandatory insulin therapy in critically ill patients using the number of episodes of hypoglycaemia and hypokalaemia per unit length of stay in intensive care. Secondary outcomes include the duration of mechanical ventilation, duration of ICU and hospital stay, hospital mortality, and measures of renal, hepatic, and haematological dysfunction.

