### Objectives

The primary objective of the study is to determine the safety of mandatory insulin infusion in critically ill patients in a general ICU setting. This will be assessed by the number of episodes of hypoglycaemia and hypokalaemia per unit length of stay in intensive care.

The secondary objectives are to investigate four mechanisms by which exogenous insulin might alter outcome: (1) effects on lipid profiles (to include free fatty acids profiles, triglyceride, HDL, and LDL levels); (2) effects on nitrogen balance; (3) effects on the somatotrophic axis; and (4) effect on oxidative damage by measuring protein carbonyls.

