### Study Definitions

*Hypoglycaemia* is defined as a blood glucose measurement taken that is less than 2.2 mmol/L (this low level is set to be in agreement with other completed and in-progress trials [5,34-38]). *Hypokalaemia* is defined as a blood potassium measurement taken that is less than 2.6 mmol/L.

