#### Outcomes

The primary outcome is to determine the number of episodes of hypoglycaemia and hypokalaemia, and compare this with the usual treatment (control) group.

Additional outcome measures used to determine safety will be duration of mechanical ventilation, duration of ICU and hospital stay, hospital mortality, and measures of renal, hepatic and haematological dysfunction. Antibiotic use will be used as a surrogate marker for nosocomial infections. Biochemical markers as specified in the protocol will also be measured to compare between groups.

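### The primary outcome is a rate per unit ICU stay, but the named chi-squared test compares event numbers, leaving out time at risk and repeat events within a patient

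*Protocol article*

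**What the plan says.** The protocol article describes the primary outcome in four places, and they do not agree.

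- **Abstract, Methods:** safety is judged by the "number of episodes of hypoglycaemia and hypokalaemia per unit length of stay in intensive care". This is a rate.
- **Objectives:** "This will be assessed by the number of episodes of hypoglycaemia and hypokalaemia per unit length of stay in intensive care". Again a rate.
- **Outcomes:** "The primary outcome is to determine the number of episodes of hypoglycaemia and hypokalaemia, and compare this with the usual treatment (control) group". The time denominator has gone.
- **Statistical Analysis:** the primary variable is the "differences in the number of hypoglycaemic and hypokalaemia events between groups which will be compared by chi-squared tests". Again there is no denominator.

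Three further statements bear on the point. Study Definitions sets hypoglycaemia as "a blood glucose measurement taken that is less than 2.2 mmol/L", and hypokalaemia likewise as a single potassium reading below 2.6 mmol/L, so events are defined per measurement. Data Collection says "Blood glucose levels will be monitored hourly" and "Data are collected for the entire period of the patient’s stay in ICU". Statistical Analysis also says "To allow for differences in length of stay between patients, wherever possible, variables will be converted to time-weighted averages" where they serve as a single between-group measure.

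**The concern.** A chi-squared test needs independent units and, for counts of events, equal exposure or an explicit allowance for it. Neither is secured here. One unstable patient can contribute several low readings, and a patient who stays longer has more chances to have one.

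ICU stay is itself listed as an outcome, and the Introduction reports a shorter ICU stay under tight control in the cited earlier study. A difference in stay is therefore a live possibility, and in a count comparison it would look like a difference in safety.

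The error can run in either direction. If mandatory insulin shortened stay by 30%, a daily event rate 1/0.70 = 1.43 times as high would give equal totals, and a comparison of totals would miss it. This is the only named primary analysis of a trial whose primary objective is safety.

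**Working it through.** **There is no figure of the plan's own to reproduce.** The protocol states no power, significance level or effect size, and the target of 120 rests on feasibility. The check therefore asks how often the named test rejects at a nominal two-sided 5% when the daily event rate is the same in both arms.

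**Inputs from the document.** 109 patients recruited (Results), taken as 55 v 54. The only event frequency is in the Discussion: 5.1% of patients in the tight-control arm of a cited study had at least one glucose below 2.2 mmol/L.

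**Assumptions, not in the document.** ICU stay is lognormal with median 6 days, log-SD 0.8 and minimum 2 days. The event rate is 0.007, 0.03 or 0.10 per patient-day; 0.007 gives about 5% of patients affected when stay is equal. Clustering is a gamma frailty, a patient-specific multiplier of the rate with mean 1 and variance 0, 1 or 3. Each scenario used 20,000 simulated trials.

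**Step 1. Chi-squared on event counts, equal stay in both arms.**

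| Events per day | Variance 0 | Variance 1 | Variance 3 |
|---|---|---|---|
| 0.007 | 0.049 | 0.060 | 0.082 |
| 0.03 | 0.077 | 0.121 | 0.209 |
| 0.10 | 0.133 | 0.268 | 0.407 |

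A more extreme case, 0.01 per day with variance 10 and 60 per arm, also leaves about 5% of patients affected and gives about 18%.

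**Step 2. Analytic check.** If the variance of the counts is φ times the Poisson variance, the true level is 2 × (1 − Φ(1.96/√φ)). For φ = 1.5, 2 and 3 this is 0.110, 0.166 and 0.258. In the cell with 0.03 per day and variance 3, the simulated variance-to-mean ratio was 2.64, which gives 2 × (1 − Φ(1.96/1.625)) = 0.228, close to the simulated 0.209.

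**Step 3. Time at risk alone.** With no clustering and a median stay 1.3 times longer in one arm, chi-squared on counts gives 0.063, 0.137 and 0.322 at the three rates. With 60 per arm the last two are about 15% and 34%.

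**Step 4. A worked illustration (hypothetical counts).** With 18 v 8 events, the expected number is 13 each, so chi-squared = 25/13 + 25/13 = 3.85, p = 0.050. If those events arose over 600 v 400 ICU days (3.0 v 2.0 per 100 days), the expected numbers are 15.6 and 10.4. Then chi-squared = 5.76/15.6 + 5.76/10.4 = 0.92, p = 0.34.

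**Step 5. Partial repairs.**

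- *Person-time denominator only.* With equal stay and variance 1 to 3, the level is still 0.096 to 0.189 at 0.03 per day and 0.210 to 0.375 at 0.10 per day. Using the number of hourly readings as denominator gives practically the same.
- *Patients with at least one event.* The level is 0.049 to 0.054 with equal stay, but 0.059 to 0.128 when one arm stays 1.3 times longer.
- *Patient-level rate test using ICU time and between-patient variance.* The level is 0.036 to 0.052 in every scenario, including a stay ratio of 1.5.

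**Step 6. What counts as an episode.** Table 1 calls for a repeat glucose after 30 minutes when a reading is below 2.6 mmol/L. One excursion can therefore yield several readings below 2.2, and the article does not say whether these are one episode or several.

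**The case against.** **The plan recognises differing lengths of stay.** It does, in the time-weighted-average sentence, and that deserves credit. But the sentence is qualified, is not tied to the event counts, and describes a quantity that a chi-squared test on counts cannot use. It does not address repeat events either.

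**The test may be meant for patients with at least one event.** This is plausible, because the cited study's 5.1% is counted that way. On that reading independence holds, and the level is near nominal when stay is equal (about 6% with a 1.3 stay ratio near the cited frequency). What stands is that the text says events, and that the proportion affected is not the rate named in the Abstract and Objectives.

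**At the cited frequency the inflation is small.** This stands for variance 0 to 3. A reader might infer that the 5.1% pins the error at about 18%. It does not: pairs from 0.007 per day with no frailty to 0.01 per day with variance 10 all leave about 5% of patients affected, so the figure cannot identify the clustering. It is also glucose only and comes from surgical ICU patients in another trial.

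**This is a pilot with no power calculation.** True, and no stated decision rule hangs on the p-value. That limits the consequence but does not make test and outcome agree.

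**Pre-randomization events.** Patients may be randomized up to 24 hours after admission, so a reader might infer that earlier events enter the count. The sentence on whole-stay data describes collection, not the analysis window, which a condensed article may leave to the full protocol. The document does not support that inference.

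**Conclusion.** The point holds as a mismatch between the stated outcome and the named test. This is not detail deferred to an analysis plan, because the article itself names the test.

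The size of the error is uncertain. It depends on event rate, clustering and stay, none of which the document gives. Under the assumed 6-day median stay:

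- with about 5% of patients affected and equal stay, type I error is about 5% to 8% for frailty variance 0 to 3, and about 18% for variance 10;
- with no clustering and a 30% longer stay in one arm, it is about 6% at that frequency, 14% at 0.03 events per day and 33% at 0.10 per day.

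The stronger statement, that the p-value will be badly wrong, is not supported: with rare events, mild clustering and similar stay it would be close to nominal. What can be said is that the test is not valid in general for this outcome, and that it does not estimate the rate the trial set out to compare.

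**What to change.** 1. In Outcomes and Statistical Analysis, use the per-unit-ICU-stay definition already given in the Abstract and Objectives.
2. State when a run of low readings counts as one episode and when a new one begins.
3. Replace the chi-squared sentence. For hypoglycaemia and hypokalaemia separately, compare episodes per patient-day, with the patient as the unit and ICU time as the denominator. Name one method that allows for between-patient variation, for example a patient-level permutation test of the rate ratio, or quasi-Poisson regression with log ICU time as offset. Report the estimate with a 95% confidence interval. One method is enough: at the cited frequency only about 6 to 10 events would be expected in all under the assumptions above, too few to support a stack of models.
4. Report the proportion of patients with at least one event as supporting.
5. Date and disclose the change, because the article says analysis is already underway and the trial is open-label.

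The cost is low. The glucose and potassium readings and the ICU stay are already collected, and nothing changes in recruitment or treatment. The price is a small amount of extra analysis and usually a wider interval.

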#### Randomization

Allocation to a treatment arm will be made randomly. A Web-based specialist randomization service will be used (www.thesealedenvelope.com). Randomization will occur once a patient meets the inclusion criteria and has either consented to the trial or his/her relative (Personal Legal Representative) has provided verbal or written assent. When a member of the trial team logs onto the randomization service, basic descriptive information will be requested. The allocation will be minimized according to the patient’s gender. The requirement to titrate an infusion of insulin in one group and an infusion of glucose in the other group, using two different schedules, precludes blinding.

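### Serial biomarkers are compared by plain analysis of variance or an undefined time-weighted average, with no stated use of the Day 1 value or gender, which gives up precision and leaves truncated series unaddressed

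*Protocol article*

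**What the plan says.** The Statistical Analysis section of the protocol article gives two methods for continuous variables measured more than once. The first is: "Differences between multiply measured continuous variables will be compared using analysis of variance". The second is meant to allow for differing lengths of stay: "variables will be converted to time-weighted averages if they are used as a single, between-group measure". The type of analysis of variance, the averaging window and any covariates are not given.

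The Data Collection section sets the schedule: "blood samples will be taken at baseline (Day 1), Day 3, Day 5, Day 7 and Day 14". Day 1 is thus labelled as the baseline. For urine: "Urine collections will be taken over the preceeding 24-hour period on Days 3, 5, and 7", so urine has no Day 1 collection. Sampling is tied to the ICU stay: "Blood and urine samples will also be taken from all randomized patients whilst they remain in the ICU". The same section records APACHE II and SOFA scores on admission. Under Randomization: "The allocation will be minimized according to the patient’s gender".

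The Objectives section shows what depends on these data: "The secondary objectives are to investigate four mechanisms by which exogenous insulin might alter outcome". The four mechanisms are lipids, nitrogen balance, the somatotrophic axis and oxidative damage.

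**The concern.** There are three separate issues, of unequal weight.

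- **Precision.** A Day 1 blood value usually explains a good part of the later values. Comparing arms without it leaves that variance in the error term. Gender was used to allocate patients but is not named in the analysis.
- **Averaging window.** If the time-weighted average runs from Day 1, part of it is measured at baseline, where no treatment effect is expected. The estimated effect is then diluted, most of all in patients with short series.
- **Truncation.** Series end at ICU discharge or death, so late samples come only from patients still in the ICU. The average puts windows of different length on one scale but takes no account of why a window ended. The Outcomes section lists ICU stay and hospital mortality among the outcomes, so the trial itself allows that treatment may affect them.

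At stake is the mechanistic evidence that the Discussion says should inform later research. The primary safety outcome is not affected.

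**Working it through.** The plan has no figure to reproduce. The Sample Size Justification states that no formal power calculation was done, and the article gives no effect size, standard deviation or correlation. The Day 1 weights below follow from the sampling days once a trapezoid rule is assumed. All other results are illustrations.

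**Inputs from the article:** blood on Days 1, 3, 5, 7 and 14; urine on Days 3, 5 and 7; target 120 patients; 109 recruited (Results).

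**Assumptions:** trapezoid averaging; an effect that is constant from Day 3 onward; the same correlation r between any two days; equal arms; two-sided 5% test; Day 1 blood drawn before treatment, as its label implies.

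**1. Precision from the Day 1 value.** Adjustment leaves a fraction 1 − r² of the variance, where r is the correlation of Day 1 with the outcome analysed.
- r = 0.5: 1 − 0.25 = 0.75, so 25% is removed.
- r = 0.7: 1 − 0.49 = 0.51, so 49% is removed.
- Equivalent patient numbers, n/(1 − r²): for the target, 120/0.75 = 160 and 120/0.51 = 235; for those recruited, 109/0.75 = 145 and 109/0.51 = 214. These assume that every patient has both a baseline and an outcome value.

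**2. Dilution if Day 1 is in the average.** The trapezoid weight of Day 1 is [(3 − 1)/2]/(last day − 1). The fraction of a constant effect that is kept is 1 minus this weight.

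| Last sample | Day 1 weight | Effect kept |
|---|---|---|
| Day 3 | 1/2 = 0.50 | 50% |
| Day 5 | 1/4 = 0.25 | 75% |
| Day 7 | 1/6 = 0.167 | 83% |
| Day 14 | 1/13 = 0.077 | 92% |

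This does not apply to urinary nitrogen, which has no Day 1 collection.

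**3. Combined effect on power.** Take an effect of 0.5 SD, r = 0.5 between days, 109 patients (54.5 per arm), and the same last sampling day for everyone. Power = Φ(δ/√(2V/54.5) − 1.96), where V is the variance of the summary in units of one reading. For a last sample on Day 7:
- Day 1 included: δ = 0.5 × 0.833 = 0.417. Weights 1/6, 1/3, 1/3, 1/6 give V = 0.5 + 0.5 × 10/36 = 0.639. Power is 78%.
- Post-baseline only: δ = 0.5. Weights 1/4, 1/2, 1/4 give V = 0.5 + 0.5 × 0.375 = 0.6875. Power is 88%.
- Post-baseline, adjusted for Day 1: V = 0.6875 − 0.25 = 0.4375. Power is 98%.

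For a last sample on Day 3 the three figures are 33%, 74% and 85%. For a last sample on Day 7, moving r from 0.3 to 0.7 takes them from 87% to 69%, from 94% to 82%, and from 97% to 99.6%.

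**4. Truncation.** A simulation with no treatment effect on the biomarker (55 per arm, 3,000 runs, r = 0.5) let the length of stay depend on the patient's underlying level. It also imposed a rise over time common to both arms, and the average included Day 1.

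| Assumed arm difference in latent stay score | Bias of average (SD) | Type I error | Bias of Day 7 samples (SD) |
|---|---|---|---|
| None | 0.00 | 5.0% | 0.00 |
| 0.3 | −0.03 | 6.0% | −0.06 |
| 0.6 | −0.06 | 7.3% | −0.12 |

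With equal stay there is no bias. With unequal stay, the arm with shorter windows averages an earlier part of the common course, and its Day 7 samples come from a differently selected group.

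**The case against.** The strongest reply is that the article condenses a fuller protocol. Model form, covariates and the handling of incomplete series are commonly left to that document or to an analysis plan, and neither is shown. This stands as far as omissions go: silence on the window or on truncation is not in itself an error. What remains is that the article does state a method, plain analysis of variance, and that a better one is available from data already collected.

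Several stronger readings are tempting and are not supported:

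- **That the average includes Day 1.** The text neither includes nor excludes it, so the dilution figures are conditional.
- **That most patients would be dropped, or standard errors understated.** The first would follow from repeated-measures analysis of variance on complete series, the second from treating all readings as independent. The article specifies neither.
- **That the length-of-stay figures show heavy attrition.** The Sample Size Justification gives 270 of 912 admissions (30%) staying 5 days or more. That covers all ICU admissions, whereas the trial enrols patients expected to need at least 48 hours, and it says nothing about Day 14.
- **That missing covariates bias the comparison.** Under randomization, omitting the baseline costs precision. Ignoring a prognostic minimization factor usually makes the test slightly conservative.

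It is also fair to say that these are secondary outcomes in a pilot, and that a mixed model does not by itself resolve truncation by death.

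**Conclusion.** The point holds as one about efficiency and incomplete series. The stated analysis leaves out a labelled baseline blood value and the minimization factor, both already collected. Under an assumed correlation of 0.5 to 0.7, this forgoes a reduction in residual variance of about 25% to 49%. A dilution to between 50% and 92% of a constant effect would be added only if Day 1 enters a trapezoid average, and never for urinary nitrogen.

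A reader might go on to infer that the mechanistic results are biased. The article does not show that. Truncation bias requires the arms to differ in ICU stay or survival. In the simulation it was modest even then, and its real size and direction cannot be determined from the article. What can be said is that averaging over unequal windows does not correct for informative truncation.

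This is an inexpensive improvement to secondary analyses, not a flaw that undermines the trial.

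**What to change.** Revise the Statistical Analysis section as follows.

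- **Blood markers:** analyse all post-baseline values in a linear mixed model for repeated measures, with treatment, day and treatment-by-day, adjusted for the Day 1 value and gender.
- **Time-weighted average, if kept:** compute it from post-baseline samples only, and compare arms by analysis of covariance on the Day 1 value and gender.
- **Urinary nitrogen:** with no Day 1 collection, adjust for gender and APACHE II.
- **Truncation:** report by arm how many patients are sampled on each day and whether series ended by discharge or death. Add a sensitivity analysis for both, because the mixed model assumes that data are missing at random.

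No new data are needed, and the cost is slightly more analysis work. The Results section says that analysis is already underway, so the change should be documented and dated before results by arm are seen. If they have already been seen, the revised analyses should be reported as post hoc alongside the stated ones.
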